# Clinical control study of traditional Chinese medicine hot compress combined with traction in the treatment of cervical spondylotic radiculopathy

**DOI:** 10.1097/MD.0000000000023880

**Published:** 2021-01-29

**Keywords:** cervical spondylotic radiculopathy (CSR), hot compress, traction

## Abstract

Cervical spondylotic radiculopathy (CSR) is the most common type of cervical spondylosis, accounting for about 60% of the incidence of cervical spondylosis. Both cervical traction and traditional Chinese medicine hot compress are common and effective treatment for CSR. This study will be performed to investigate the effect of a combination of cervical traction and traditional Chinese medicine hot compress on CSR. In this non-blinded, randomized controlled trial, 100 eligible patients will be randomly divided into a treatment group (intermittent cervical traction combines with traditional Chinese medicine hot compress) and a control group (intermittent cervical traction combined with hot compresses). Before and after the intervention, the Visual Analog Scale score, Neck Disability Index score, and 20-score scale of symptoms will be evaluated at baseline and at 7, 14, 21, and 28 days. During the treatment period, any signs of acute adverse events, such as paralysis of aggravated pain, nausea, dizzy, and even syncope, will be recorded at each visit. Although intermittent cervical traction and traditional Chinese medicine hot compress have been used in the treatment of CSR in China for many years, there is no consensus on its effectiveness of combination therapy. This experiment will provide convincing evidence of the efficacy of intermittent cervical traction combined with traditional Chinese medicine hot compress in the treatment of CSR.

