#### Outcome measurement

2.1.6

Pain is one of the most common reasons for patients with CSR to see a doctor. Therefore, the Visual Analog Pain Scale (VAS) will be chosen as the main outcome measure for the assessment of the neck and upper limbs. The VAS score is a reliable and effective method of pain measurement. There is a 100 mm long horizontal line. The left side records “no pain” (score 0), and the right side records “pain is severe and intolerable” (score 10). The patient is required to place a mark corresponding to its current pain level on the horizontal line (the most severe pain at rest and during exercise),^[11]^ and then determine the VAS score by measurement.

Neck Disability Index (NDI)^[12]^ is one of the most commonly used indexes to evaluate patients neck dysfunction. The NDI score includes 4 subjective symptoms (neck pain intensity, headache, concentration, sleep) and 6 items related to activities of daily living (weightlifting, work, driving or cycling, entertainment, personal care, reading). Each item has 6 levels of responses, each with a score of 0 to 5, 0 means no disability, 5 means severe disability. The lowest total NDI score is 0 points, and the highest is 50 points; the higher the score, the more serious the degree of dysfunction. This study adopted all dimensions of NDI score.

Tanaka Yasuhisa Cervical Spondylopathy Symptom Scale is the “Nerve Root Cervical Spondylopathy Symptom Scale” proposed by the Japanese scholar Hisasu Tanaka. It compares the improvement index before and after treatment for evaluation: improvement rate = (points after treatment-points before treatment)/(20 -Points before treatment)∗100%.

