#### Data collection and monitoring

2.2.2

This is a 4-week clinical trial. Participants need to conduct a 4-week research intervention during a 4-week follow-up. Five rounds of disease activity assessment (baseline and week 1, 2, 3, and 4) will be independently recorded by 2 investigators in Epidata (version 3.1), and differences will be resolved through discussion and a third research institute. Longhua Hospital affiliated to Shanghai University of Traditional Chinese Medicine is responsible for monitoring and quality control.

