#### Quality control

2.2.3

Before conducting the study, we will conduct unified training to ensure that all relevant doctors, nurses and evaluators fully understand the entire trial process. In order to ensure the quality of the entire study, 2 supervisors will be sent every month to ensure that the enrolled patients meet the inclusion criteria and do not meet the exclusion criteria; the research group recruits enough patients to participate in the study; all enrolled patients fully follow the clinical trial Process, perfect the case report form (CRF), follow the standard operating procedure (SOP). During the entire treatment and follow-up period, the inspector will record the dropout, withdrawal, and related reasons in detail, and record any compliance of all patients.

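### The trial is declared non-blinded and describes no masking of evaluators, recorders or statisticians, although its main outcome is a patient-marked pain scale and staff-side bias could be limited at low cost

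*Protocol article*

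**What the plan says.** The blinding status is given once, in the Abstract: "In this non-blinded, randomized controlled trial, 100 eligible patients will be randomly divided". No role is exempted there, and sections 2.1.5 to 2.2.3 are silent on masking.

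- **Outcome (2.1.6):** "the Visual Analog Pain Scale (VAS) will be chosen as the main outcome measure for the assessment of the neck and upper limbs". On rating, the article says "The patient is required to place a mark corresponding to its current pain level on the horizontal line"; the score then comes from measuring that mark ("then determine the VAS score by measurement"), by a reader who is not named.
- **Interventions (2.1.4):** the control arm gets a heated bag that belongs to the traction device. The other arm gets a pack of herbs that are soaked and steamed.
- **Recording (2.2.2):** two investigators record each assessment independently in Epidata, and "differences will be resolved through discussion and a third research institute".
- **Evaluators (2.2.3):** they appear as a role of their own in the training plan, which is to ensure that "all relevant doctors, nurses and evaluators fully understand the entire trial process".
- **Analysis (2.2.1):** trained statisticians apply a t test to normally distributed variables and nonparametric tests otherwise. Their knowledge of the arms is not addressed.

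**The concern.** The main outcome is subjective. The Neck Disability Index and the 20-point symptom scale also rest largely on reported symptoms and function. Patients and therapists can tell a steamed herbal pack from a device bag, so masking them may not be feasible. That reason does not extend to everyone else who handles the outcome.

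Staff can influence a VAS result at four points:

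- **Instruction.** Section 2.1.6 asks for current pain but adds, in brackets, the worst pain at rest and in movement, and covers both neck and upper limbs. Whoever explains the line can affect which pain is marked.
- **Reading.** Someone measures the mark.
- **Recording.** Two people enter the value, and differences between them are settled.
- **Analysis.** A test is selected, and no single primary time point is named among the four post-baseline assessments.

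If the people at these points know the arm, small pulls in one direction can add to the patients' own expectation. At stake is how far a positive result can be credited to the herbs, when the Abstract promises evidence that will convince.

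**Working it through.** **Step 1. Does the article mask anyone?** The table sets the roles against the text.

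| Role | Where named | Masking stated? |
|---|---|---|
| Patient (marks VAS) | 2.1.6 | No; the Abstract says non-blinded |
| VAS reader | 2.1.6, not identified | No |
| Evaluators | 2.2.3, listed beside doctors and nurses | No |
| Two recording investigators | 2.2.2 | No |
| Third research institute | 2.2.2 | No |
| Statisticians | 2.2.1 | No |

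The only statement on blinding is the unqualified one in the Abstract. The body neither confirms nor limits it for any role.

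**Step 2. How sensitive is a trial of this size to bias?** The plan gives no figure to reproduce: the heading for the sample size calculation (2.2) has no effect size, SD or power beneath it. The inputs are:

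- 50 patients per arm (2.1.5);
- two-sided 5% level (2.2.1);
- a systematic between-arm bias b, in SD units, from 0 to 0.4. This range is an assumption; the document gives neither a VAS SD nor a bias size.

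The standard error of the mean difference, in SD units, is √(2/50) = 0.20. With no true effect, and using the normal approximation:

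P(reject) = Φ(b/0.20 − 1.96) + Φ(−b/0.20 − 1.96)

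| Assumed total bias b (SD) | b/0.20 | P(reject) |
|---|---|---|
| 0 | 0 | 5.0% |
| 0.1 | 0.5 | 7.9% |
| 0.2 | 1.0 | 17.0% |
| 0.3 | 1.5 | 32.3% |
| 0.4 | 2.0 | 51.6% |

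For comparison, 50 per arm detects (1.96 + 0.84) × 0.20 = 0.56 SD with 80% power. A bias of 0.2 SD is about a third of that (0.2/0.56 = 0.36).

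**Step 3. What do these figures measure?** They measure total bias from any source. Total bias is the patient part plus the staff part, and masking staff removes at most the second. The document offers nothing from which to split the two. Since the patient makes the mark and staff only explain, measure and record it, the patient part is probably the larger.

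**The case against.** The strongest reply is that a condensed article need not spell out coded data entry or masked analysis, and that the word non-blinded may describe only patients and therapists. This stands in part: details of coding may well sit in a fuller document. But the article does not merely stay silent. It declares a blinding status and exempts nobody, so the reader is given a design choice with no limit on it.

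Second, the VAS is marked by the patient, measuring a mark leaves little discretion, and no prompting is described. This stands as a limit on what masking staff can gain.

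Third, the schedule in 2.1.2 has recruitment ending in December 2020 and follow-up ending on January 31, 2021, while the article is dated January 29, 2021. On those dates, changes to VAS collection could hardly take effect. Masked analysis and a stated limitation still could.

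A reader might also draw stronger conclusions that the document does not support:

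- **That every role is known to be unmasked throughout.** This is an inference from one word in the Abstract; the body states no role's status.
- **That unmasked staff settle the discrepancies.** Section 2.2.2 also involves a third research institute, whose masking is unstated. Nor does it say that the original line is not consulted.
- **That statisticians pick the test freely once they see the arms.** Section 2.2.1 sets a rule in advance that depends on distribution, not arm. The rule is loose, but that is a separate matter.
- **That masking would cost nothing.** The document does not show that evaluators or recorders are separate from treating staff.

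**Conclusion.** The point holds in a limited form. The article declares the trial non-blinded, relies on a patient-marked pain scale with recognisably different compresses, and describes no masking of evaluators, recorders or statisticians. Limiting staff-side bias is a reasonable request, and so is saying plainly what bias remains.

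The size of the gain cannot be given. An assumed total bias of 0.1 to 0.3 SD would take the false-positive rate from 5% to between about 8% and 32%, so modest bias matters with 50 per arm. A reader might take these figures as the benefit of masking staff; they are not. They rest on an assumed range for bias from all sources, and bias from patients who know their arm would remain after the change. That remaining part is the main reason to moderate the Abstract's claim.

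**What to change.** 1. Have patients complete the VAS alone and out of the therapist's sight.
2. Use the evaluators already named in 2.2.3 as outcome assessors unaware of arm, where they are not treating staff. Where that is not possible, say so.
3. Label the arms A and B for the two recording investigators and the statisticians until the database is locked and the analysis is complete.
4. Resolve recording differences under 2.2.2 against the original VAS line.
5. State in the methods that the trial is open-label for patients and therapists, that patient-expectation bias therefore remains, and qualify the Abstract's promise about the strength of the evidence.

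If outcome collection is already finished, items 3 (for the analysis), 4 (if the marked lines were kept) and 5 can still be done.

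The sample size, significance level and treatments do not change, and no extra staff should be needed if duties can be separated. The cost is minor logistics. Masking of evaluators will be imperfect, for example if herb odour reveals the arm.

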## Introduction

1

Cervical spondylosis is a syndrome in which degenerative changes or secondary changes of cervical intervertebral discs stimulate nerve roots, spinal cord, vertebral arteries, or sympathetic nerves, etc., which cause related symptoms and signs.^[1]^ Cervical spondylotic radiculopathy (CSR) is the most common type of cervical spondylosis, accounting for about 60% of the incidence of cervical spondylosis.^[2]^ The treatment methods of CSR are mainly divided into surgical treatment and conservative treatment. Surgical treatment is not considered as the first choice for CSR. At present, there are a lot of nondrug conservative treatment methods, such as acupuncture, massage, Daoyin exercises, traditional Chinese medicine compresses, low-frequency therapy, microwave, etc., and they all have certain treatments for CSR. In the literatures,^[3]^ the clinical efficacy of conservative treatment and surgical treatment is equivalent. Therefore, it is great significant to explore how to use the optimal combination of conservative treatments to improve the neck pain and radicular symptoms of patients with radiculopathy, and alleviate the progress of cervical spondylosis.

Cervical traction is a common and effective treatment for CSR. Traction relieves the stimulation and compression of nerve roots according to improving the mechanical balance of the cervical spine, changing the relationship between disc protrusions or osteophytes and surrounding tissues. What the functions of intermittent traction are concluded^[4–6]^:

1.The force of intermittent traction is greater than the continuous traction, which is more conducive to stretch the intervertebral space and intervertebral foramen and relieve symptoms.2.Intermittent traction can also cause the neck muscles to have a rhythmic alternating movement of tension and relaxation, resulting in a local massage effect, which is more conducive to relieve neck muscle spasm and eliminate inflammation around the nerve root.3.Intermittent traction can restore muscles and blood vessels, and fewer symptoms such as headaches and nausea after traction, reduce the long-term direct compression of local muscles and blood vessels by the traction belt during traction, and reduce reflex caused by muscle and vasospasm. It is more likely to be accepted by patients.4.In the process of intermittent traction, the muscles are relaxed and combined with work and rest, which reduces the possibility of continuous traction to the neck and back muscles and better relieves muscle spasms.

Traditional Chinese medicine hot compress is to directly place the herbal hot pack directly on the neck, exerting the thermal effect, heating up local tissues, expanding capillaries, accelerating blood circulation, improving local metabolism, and achieving the effects of anti-inflammatory, swelling, and reflex muscle spasms. It relaxes the muscles, relieves fatigue and pain,^[7]^ and restores the balance of the dynamic system. And hot compress is with the help of the warming effect to bring the effective ingredients of traditional Chinese medicine into the meridians and collaterals directly to the location of disease, and form a higher concentration in the neck area, fully synergizing the warming and pharmacological effects, so as to achieve the effects of warming the meridian, promoting blood circulation and relieving pain. This project intends to conduct a prospective randomized controlled trial of herbal hot compress combined with traction for the treatment of CSR patients to verify the effectiveness and safety of hot compress combined with traction for CSR treatment.

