#### Randomization and allocation

2.1.5

After screening, patients will be randomly divided into 2 groups with a 1:1 allocation ratio. Randomization will be based on the Statistical Social Science Software Package (SPSS) software (version 21.0), generating random numbers, and patients will be randomly divided into treatment group (50 cases) and control group (50 cases).

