#### Statistical analysis

2.2.1

Trained statisticians will use intentional processing methods for effectiveness and safety analysis. In addition, the final outcome observation index method will be applied to deal with missing values. All statistical analysis will be performed by the SPSS 21.0. The statistical test is two-way, *P* < .05 is statistically significant. The mean ± standard deviation will be used to describe continuous variables. This percentage is used to describe the variable. Continuous variables that follow a normal distribution will be analyzed by Student *t* test; otherwise, nonparametric tests will be used to compare group differences.

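### The stated aim of verifying safety is beyond 50 patients per arm, which can only describe common adverse events: none in 50 still leaves a 95% upper limit of 7.1%

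*Protocol article*

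**What the plan says.** The last sentence of the Introduction sets the aim as "to verify the effectiveness and safety of hot compress combined with traction for CSR treatment". The Abstract, the opening of section 2 and the Discussion speak only of effect or efficacy, so the safety aim appears in that one place.

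The size is fixed in the Abstract ("100 eligible patients will be randomly divided into a treatment group") and in section 2.1.5: "patients will be randomly divided into treatment group (50 cases) and control group (50 cases").

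Section 2.1.4 states that the intervention group has the same traction method as the control group. The arms differ in the compress.

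On adverse events, the Abstract says that "any signs of acute adverse events, such as paralysis of aggravated pain, nausea, dizzy, and even syncope, will be recorded at each visit". Section 2.1.7 has side effects recorded at each treatment visit. The article gives no expected event rate, tolerable rate or precision target.

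Section 2.2.1 covers both analyses in one sentence: "Trained statisticians will use intentional processing methods for effectiveness and safety analysis". It then says "The statistical test is two-way", sets the 0.05 level, names tests for continuous variables, and mentions percentages as a description.

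**The concern.** To verify safety is to show that harms are rarer than some level that matters. The article sets no such level, and 50 patients per arm can exclude only fairly high rates. Three features bear on this.

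- **Size.** An event affecting one patient in 50 or one in 100 may well not occur at all in an arm. Its absence would say little.
- **Shared exposure.** Events such as dizziness or syncope may come from traction, which both arms receive. Equal rates in the two arms fit a low or a high incidence equally well.
- **Denominator.** If every randomised patient is in the safety denominator, anyone who never had a session counts as event-free, and the observed rate falls.

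What is at stake is the conclusion the trial may draw. The Discussion wants to explore whether the combination could become a first choice among conservative treatments, so a safety claim stronger than the data allow could influence practice.

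**Working it through.** **Inputs from the article.** n = 50 per arm and 100 in total (Abstract, section 2.1.5); two-sided 0.05 level (section 2.2.1). There is no event rate or safety figure in the article to reproduce. The upper limits need no assumed rate. Every event rate below is an assumption, used for illustration.

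**1. What zero events would exclude.** With 0 events in n patients, the exact (Clopper-Pearson) two-sided 95% upper limit is 1 − 0.025^(1/n).

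- One arm: 1 − 0.025^(1/50) = 0.071, or 7.1%.
- Both arms pooled: 1 − 0.025^(1/100) = 0.036, or 3.6%. This is relevant only to events from what the arms share.
- One arm, one-sided 95%: 1 − 0.05^(1/50) = 0.058, or 5.8%. The choice of convention does not change the conclusion.
- With 45 evaluable patients in an arm (assumed), the two-sided limit is 7.9%; with 40 (assumed), 8.8%.

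**2. Chance of seeing an event at all in one arm.** The probability of no event is (1 − p)^50.

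| Assumed true rate | No event in 50 | At least one |
|---|---|---|
| 1% | 60.5% | 39.5% |
| 2% | 36.4% | 63.6% |
| 5% | 7.7% | 92.3% |

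Common reactions will be seen. Uncommon ones often will not.

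**3. What an arm comparison could show.** The article names no test for event counts, so this is an illustration. With a events in 50 against 0 in 50, the two-sided Fisher P is 2 × C(50,a)/C(100,a).

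- a = 5: 2 × 2,118,760/75,287,520 = 0.056.
- a = 6: 2 × 15,890,700/1,192,052,400 = 0.027.

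Six affected patients against none would be needed to pass 0.05. At assumed true rates of 10% and 2%, exact Fisher power is 19%. For an event caused by the shared traction, the expected arm difference is zero whether the common rate is 1% or 20%, so no arm comparison at any sample size estimates that rate.

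**4. Denominator.** If 5 of 50 patients never start (assumed; the article gives no figure), the rate is multiplied by 45/50 = 0.90. One affected patient is then 1/50 = 2.0% instead of 1/45 = 2.2%. This is small beside the 7.1% in step 1.

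**The case against.** **Safety is secondary here, and the limit is generic.** The stated purpose elsewhere is efficacy, pain on the VAS is the main outcome, and any trial with 50 per arm has the same 7.1% limit. This is fair and keeps the point modest. It does not rescue the verb: the article states a safety aim that its own size cannot meet for uncommon events.

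**A safety set and exact intervals belong in an analysis plan.** Their absence from an article is no fault. But section 2.2.1 is not silent: it places safety under the same rule as effectiveness, and that stated rule is what needs changing. The article's phrase is garbled. Intention-to-treat is the likely reading, not a certain one, and the main point does not depend on it. The right to withdraw at any time does not show that anyone will miss every session.

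**Stronger readings that the text does not support.** A reader might infer that P < .05 is the decision rule for safety and that a null comparison would be reported as the combination being safe. The article says neither. Section 2.2.1 names tests only for continuous variables, and its mention of percentages is already close to descriptive reporting. A reader might also take paralysis to be a listed event, but the Abstract's wording there is garbled; syncope is clear. Nor is it right that the trial can say nothing on safety: a 5% event would very probably be seen.

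**Conclusion.** The point holds as one about the strength of the safety aim and the population for the safety analysis. With 50 per arm, zero events of a given type leaves rates up to 7.1% compatible with the data in one arm, and up to 3.6% when both arms are pooled for traction-related events. These figures rest only on the stated sample sizes and the two-sided 95% convention, with every patient evaluable; losses would raise them. The Fisher and detection figures rest on assumed rates or counts. The denominator effect depends on reading the garbled phrase as intention-to-treat and on an unknown number of patients who never start; it is probably small. The severity is minor to moderate: no endpoint, named test or patient number is wrong, but what the trial may conclude about safety changes.

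**What to change.** - **Introduction:** restate the safety part of the aim as describing adverse events.
- **Section 2.2.1, population:** separate safety from effectiveness. Analyse safety in patients who received at least one session, grouped by treatment received.
- **Section 2.2.1, reporting:** give each event type as the number of patients affected, with an exact 95% confidence interval per arm. For events attributable to the shared traction, add the same figures pooled across arms.
- **Section 2.2.1, interpretation:** add a sentence that a non-significant difference between arms will not be read as evidence of safety.

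The cost is some rewording and a few table rows, with no new patients, visits or data items, provided that sessions received are recorded. The downside is a more modest safety claim.
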